## 8. Duration of Treatment

The anticipated duration of treatment will be 5 years for both the dysplasia component and the general population component. Relying on existing population rosters and on the Linxian esophageal cancer registry, it will be possible to follow total mortality and total esophageal cancer incidence and mortality for the entirety of both cohorts, including those who never enroll and those who drop out of the study.

## 9. Statistical Considerations

### (a.) Sample size

The total population aged 40-69 in the three communes in which the study will be conducted numbers 33,643, based on the national census conducted in China in 1982. In December 1983, a mass screening of esophageal cytology by balloon swallow was conducted by the CI among 12,000 adults age 40-69 in these communes. The cytology slides are still being scored, but preliminary results indicate that 20% of those screened have severe esophageal dysplasia (see Appendix 1, Cytologic Diagnosis of Dysplasia). At this percentage, approximately 2,400 dysplasia patients will be identified as potential subjects for the dysplasia trial.

It is proposed to enroll all eligible persons in the general population and in the dysplasia trials. From our pilot study, we estimate that 90% will be eligible and willing to participate in the trials. Thus, there will be 2,160 participants in the dysplasia trial and approximately 28,000  $[(33,643 - 2,400) \times .9]$  in the general population trial.

### (b.) Power

The following assumptions were made in the power calculations:

- (1) The annual crude esophageal cancer mortality rate in persons aged 40-69 in the general population trial is  $650 \times 10^{-5}$  (or 0.65% per year);
- (2) The annual mortality from esophageal cancer in patients with severe dysplasia age 40-69 is 1.78%;
- (3) Excluding events in the first 6 months, the rates in the following 4 1/2 years will be 2.9% for the general population and 8.0% for those with dysplasia.
- (4) The effect of drop-outs and competing risks is ignored; and
- (5) Alpha error (one-sided) is set at 0.05.

For the dysplasia trial, with  $P_0 = .08$  and 1,080 persons in each treatment arm; the detectable differences and power are shown below:

1.690/gv

| P1      | Decrease
due to intervention | Power |
|---------|---------------------------------|-------|
| 0.064   | 20%                             | 42%   |
| 0.060   | 25%                             | 57%   |
| 0.056   | 30%                             | 72%   |
| 0.052   | 35%                             | 84%   |
| → 0.048 | 40%                             | 93%   |
| 0.044   | 45%                             | 97%   |

For the general population trial, with  $P_0 = .029$  and 14,000 per treatment arm and assuming a 2 group trial for simplicity of calculation; detectable differences and power are:

| P1       | Decrease
due to intervention | Power |
|----------|---------------------------------|-------|
| 0.0247   | 15%                             | 72%   |
| → 0.0232 | 20%                             | 92%   |
| 0.0218   | 25%                             | 99%   |

These estimates are based on the formula (see e.g. ref [33]).

(INSERT FORMULA)

$$\phi = \left[ \frac{-Z_{\alpha} (A+B) + \sqrt{N_0 (A+B)} |P_1 - P_0|}{\sqrt{(A+B)(RA-B) - R(P_1 - P_0)^2}} \right]$$

where  $P_1$  = outcome proportion in the index series

$P_0$  = outcome proportion in the comparison series.

$R$  = ratio of size of comparison series to size of index series

$N_0$  = size of comparison series

$Z_\alpha$  = value of standard normal deviate corresponding to desired alpha-level of the test

$$A = P_1(1-P_0) = P_0(1-P_1)$$

$$B = (R-1) P_0(1-P_0)$$

$\phi$  = distribution of a standard normal deviate(32)

Thus, the dysplasia trial will be able to detect with high power a 40% reduction in esophageal cancer rates associated with the intervention, and the general population trial, a 20% reduction. The power of the general population trial (which will use a fractional factorial design---see Section D.4) to detect differences associated with individual factors will vary under various possible alternative outcomes, but will be high to evaluate differences of 20-30% due to each factor under a number of plausible outcomes. Because the number of deaths due to esophageal cancer will be lower than the number of incident esophageal cancer cases, total cancers, and total mortality, power for looking at these other outcomes of interest (not shown here) will be greater.

#### (c.) Data Analysis

The methods of analysis to be applied to the data collected during these trials include simple contingency table analysis and Cox's method of regression analysis for survival data.(34) The use of regression methods will allow for incorporation of variables stratified on at randomization and adjustment for risk factors which are found by the initial interview to be nonrandomly distributed between treatment groups.

Analysis of the dysplasia trial data will allow us to make a statement about the effect of the combined multivitamin-multimineral preparation only, while in the general population trial we will be able to separate out the effects of the several factors.

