#### D. Experimental Design - Intervention Plan

##### 1. Participant Selection

###### Inclusion Criteria (both interventions):

- a. Limited to 3 northern communes (Yaocun, Rencun, and Donggang).
- b. Males and females aged 40-69.
- c. Able and agree to participate for duration of trial.

In addition, for the dysplasia trial only, persons must have been found to have severe (group 1 or 2) dysplasia in a mass balloon cytology screening conducted in the fall of 1983.

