## 3. Intervention Assignment

### Dysplasia Component

Participants will be recruited from among residents of Yaocun, Rencun and Donggang communes identified as having severe esophageal dysplasia in the December 1983, balloon-swallow cytology screening. The identification and interviewing of dysplasia patients is expected to take one month. All eligible dysplasia subjects who complete the pre-study requirements will be randomized by individual in blocks of 8 into treatment (or placebo) groups, stratified by age (5-year groups), sex, and commune. Actual enrollment of subjects for the dysplasia trial is expected to take an additional 2 months to complete.

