### General Population Component

Participants will be recruited from census lists of eligible residents aged 40-69 from three communes (Yaocun, Rencun, and Donggang) in northern Linxian (excluding those already taking part in the dysplasia component). Census figures indicate that the current population of the 3 target communes for males and females age 40-69 is 33,643.

The pre-study evaluation for these subjects is expected to take 2-3 months and will be started after the dysplasia trial accrual is complete. Those eligible and completing pre-study requirements will be randomized by individual in blocks of 8 into treatment (or placebo) groups, stratified by age (5 year groups), sex, and commune. Accrual for the general population trial is expected to take 4 months to complete.

For both the dysplasia and the general population components, randomization will be conducted in Beijing and the key will be kept at NCI so as to keep the trial double blind for all involved persons in Linxian and Beijing.

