During the interventions, 400 study subjects per year will be selected at random to have blood and urine collected and have a dietary history and anthropometric measurements taken. Blood will be analyzed for the various vitamins and minerals being administered during the trials and urine will be analyzed for nitrosamines (see Table 7 below). This surveillance will include participants from both trials limited to those who had samples collected before the onset of pill-taking and will be performed throughout the year (100 persons every 3 months; 20 from dysplasia trial, 80 from general population trial).

The laboratory analyses for this surveillance program will be performed in China with a 10% sample being sent to the U.S. for simultaneous analysis as a part of an ongoing quality control program.

In addition to assessing compliance and seasonal/secular changes, baseline measurement of nutrients in all dysplasia trial participants will allow us to adjust for any non-random differences between treatment groups and review our outcomes by baseline nutrient status.

Table 7

Laboratory analyses to be conducted during the trials.

| Analyte | Tissue               | Method                             |
|----------------|-----------------------------|-------------------------------------------|
| Retinol        | Plasma                      | HPLC                                      |
| Carotenoids    | Plasma                      | HPLC                                      |
| Tocopherol     | Plasma                      | HPLC                                      |
| Riboflavin     | Erythrocytes                | Glutathione reductase
activity         |
| Niacin         | Urine                       | Spectrophotometric                        |
| Ascorbic acid  | Plasma                      | Spectrophotometric                        |
| Molybdenum     | Erythrocyte,
hair, nails | Spectrophotometric                        |
| Selenium       | Erythrocyte,
hair, nails | Spectrophotometric,
neutron activation |
| Zinc           | Plasma, hair                | Spectrophotometric                        |
| Cholesterol    | Plasma                      | Spectrophotometric                        |

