#### 10. Records to be Kept

The CICAMS will develop, in collaboration with NCI, questionnaires and forms needed for the collection, storage, and coding of data. All questionnaires and recording forms used in the study will be developed in both Chinese and English-language versions, and will be reviewed by NCI before being used in the study.

Questionnaires and forms will include the following:

- 1) a brief questionnaire for all study participants, containing personal identifiers, demographic information (age, sex, production brigade), information necessary to confirm the subject's eligibility (for example, whether the person is taking vitamin supplements or other medicines regularly), and several items concerning risk factors such as family history of esophageal cancer patterns of consumption of pickled vegetables or moldy foods and cigarette smoking status;
- 2) a cytology abstract and follow-up form for all those included in the 1983 balloon-swallow mass screening, with space for such information as name, date of birth, sex, commune of residence, study ID if eligible for study, initial cytological diagnosis, and any subsequent cytological diagnosis during the course of the study;
- 3) a form to collate information on all persons considered for the trials, with space for such information as name, date of birth, sex, production brigade of residence, study ID if eligible (or reason ineligible), whether enrolled (or reason if not enrolled), biochemical test status and results, compliance information during the course of the study, and vital status at the completion of the study, with date and cause of death if deceased;
- 4) logs necessary to perform such tasks as:  
assignment of identification numbers, randomization, enrollment, tracking, and distribution of pill packs, reclamation of used pill packs, chronicling of barefoot doctors' visits with participants, noting of pill counts for the purpose of compliance assessment, and recording of dates and causes of death;
- 5) questionnaires and recording forms needed:
  - a) to conduct a biochemical surveillance program to monitor secular and seasonal changes in nutritional status and diet within and among treatment groups, and b) to perform biochemical tests for the purpose of compliance assessment;
- 6) coding sheets listing all of the data collected for each individual, reviewed and edited for completeness and accuracy;

7) logs necessary to maintain quality control of data, including:

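### Beyond the stratification variables, adjustment is tied to observed baseline imbalance, which selects covariates on chance and does not cover baseline cytology; name the covariates in advance instead

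*Protocol*

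**What the plan says.** Section D.9(c) of the Protocol names contingency tables and Cox regression as the methods. It gives regression two uses.

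- **Stratification variables:** "The use of regression methods will allow for incorporation of variables stratified on at randomization". Section D.3 identifies them: "stratified by age (5-year groups), sex, and commune" in the dysplasia trial, and the same three in the general population trial. No condition on imbalance is attached.
- **Interview risk factors:** "adjustment for risk factors which are found by the initial interview to be nonrandomly distributed between treatment groups". Here imbalance is the stated ground for adjusting.

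Section D.7 says that baseline nutrient measurements in all dysplasia trial participants will let the investigators "adjust for any non-random differences between treatment groups and review our outcomes by baseline nutrient status".

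Section D.10, item 1, lists the interview risk factors by example: family history of esophageal cancer, pickled or moldy foods, and smoking. Cytology is held elsewhere, under item 2: "a cytology abstract and follow-up form for all those included in the 1983 balloon-swallow mass screening". The dysplasia trial admits two cytology groups: "persons must have been found to have severe (group 1 or 2) dysplasia".

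**The concern.** Both trials randomise individuals in blocks of 8. If that is done correctly, no baseline factor is nonrandomly distributed between groups, and any difference seen is chance. In practice the provision therefore means looking for imbalance and adjusting for what stands out. A covariate enters because of the luck of the allocation, not because it predicts esophageal cancer death. A strongly prognostic but balanced covariate stays out.

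Two consequences follow. First, no test, threshold or variable list goes with the trigger, so the model is settled only once data are in hand. Sections D.7 and D.9(d) have outcomes examined annually by treatment group, so the choice could be made with outcomes visible. Second, neither use of regression in D.9(c) reaches baseline cytology, although the protocol's own mortality assumptions treat severe dysplasia as carrying much higher risk.

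**Working it through.** **1. The plan's own power figures.** Inputs from D.9(b): one-sided alpha 0.05; control risk 8.0% with 1,080 per arm (dysplasia); control risk 2.9% with 14,000 per arm (general population, treated as two groups). For two proportions with pooled variance under the null:

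power = Φ{[|P0 − P1| − 1.645·√(2p̄(1−p̄)/n)] / √[(P0(1−P0) + P1(1−P1))/n]}

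For 8.0% against 4.8%: p̄ = 0.064, so (0.0320 − 1.645 × 0.01053)/0.01051 = 1.40, giving 91.9% (stated 93%). For 2.9% against 2.32% the result is 91.9% (stated 92%). All nine printed rows reproduce within 2 points. These are unadjusted comparisons, so the stated power does not depend on the covariate rule.

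**2. How often chance triggers adjustment.** The protocol gives neither a threshold nor a count of factors. Assume a 5% test and k independent tests: P(at least one flag) = 1 − 0.95^k.

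- k = 3: 14%
- k = 5: 23%
- k = 10 (the number of analytes in Table 7, if all were screened): 40%
- k = 20 (five factors over the four factorial contrasts): 64%

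Any one covariate is flagged in only about 5% of trials, however prognostic it is.

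**3. What the rule costs.** Simulation at the dysplasia trial's size: 1,080 per arm, control risk 8%, 200,000 runs per scenario. There was one binary covariate; its prevalence (30% or 50%), its odds ratio and the two-sided 5% imbalance test are assumptions. Always adjusting (Mantel-Haenszel) was compared with adjusting only when the imbalance test is significant. Entries are percentages for prevalence 30% / 50%.

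| Odds ratio | Type I error, rule followed | Type I error, better result picked | Power at 40% reduction: rule | Power at 40%: always adjust | Power at 30% reduction: rule | Power at 30%: always adjust |
|---|---|---|---|---|---|---|
| 1.5 | 4.99 / 4.96 | 5.24 / 5.18 | 92.02 / 92.21 | 92.11 / 92.27 | 71.67 / 71.74 | 71.81 / 71.98 |
| 3 | 4.96 / 4.95 | 5.66 / 5.57 | 92.14 / 92.23 | 92.49 / 92.54 | 71.70 / 71.63 | 72.47 / 72.33 |
| 5 | 4.88 / 5.01 | 5.91 / 5.87 | 92.15 / 92.30 | 92.91 / 92.86 | 71.87 / 71.75 | 73.37 / 72.94 |

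The largest gain from always adjusting is 92.91 − 92.15 = 0.76 points at a 40% reduction and 73.37 − 71.87 = 1.50 points at 30%.

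**4. Is cytology prognostic on the plan's figures?** D.9(b) assumes annual esophageal cancer mortality of 1.78% with severe dysplasia and 0.65% in the general population trial: 1.78/0.65 = 2.7.

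In the general population trial the relevant variable is 1983 screening status. D.9(a) gives 33,643 residents, 12,000 screened and 20% found positive (2,400). Assume that the unscreened have the same 20% prevalence, that screening misses no one, and that undetected dysplasia carries 1.78%.

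- Unscreened: 33,643 − 12,000 = 21,643, of whom 20%, or 4,329, have undetected dysplasia.
- Share of the trial's source population: 4,329/(33,643 − 2,400) = 13.9%.
- Rate without dysplasia: (0.65 − 0.139 × 1.78)/0.861 = 0.47%.
- Rate in the unscreened: 0.2 × 1.78 + 0.8 × 0.47 = 0.73%.
- Ratio, unscreened to screened-negative: 0.73/0.47 = about 1.6.

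No separate mortality figure is given for group 1 and group 2 dysplasia, so the same calculation cannot be made within the dysplasia trial.

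**The case against.** The text is permissive. It says what regression will allow, names no primary model, and does not say that only unbalanced factors may be adjusted for. It can be read as a safeguard in case allocation goes wrong in the field. Naming covariates and the primary model is commonly left to a statistical analysis plan, which may exist but is not shown. Followed mechanically, the rule does no measurable harm to type I error.

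Much of this stands, and it limits the size of the point. But the imbalance trigger is a stated ground for adjustment, not an omission, and it appears twice; an analysis plan that followed it would inherit it. If failed allocation is the worry, a check of the allocation can be kept apart from the choice of model.

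A reader might infer more than the documents support:

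- **That the strongest prognostic variables are missed.** The same sentence of D.9(c) provides for age, sex and commune, and the protocol ranks no variable by prognostic strength. Only cytology can be said to be both outside the provision and prognostic on the plan's figures, and then only between the two populations.
- **That the standard error will be wrong.** This presumes an unstratified primary test, which the protocol does not specify.
- **That the risk ratio by screening status is nearer 1.8.** This needs 0.65% to be the whole-population rate: (0.65 − 0.2 × 1.78)/0.8 = 0.37%, and 0.65/0.37 = 1.8. D.9(b) attaches 0.65% to the general population trial.

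**Conclusion.** The point holds in limited form. For interview risk factors and, in the dysplasia trial, baseline nutrients, the protocol ties adjustment to observed imbalance. After correct randomisation that selects on chance, leaves the final model open, and passes over baseline cytology.

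The numerical effect is minor. One-sided type I error is 4.9-5.0% if the rule is followed and 5.2-5.9% if the more favourable of two results were chosen afterwards, which the protocol does not propose. Power forgone is at most about 0.8 points at the 40% design effect and 1.5 points at 30%, at an assumed odds ratio of 5. These results are for a two-arm trial of the dysplasia trial's size with one binary covariate; the general population trial was not simulated. The 23% and 64% flag rates and the 1.6-fold ratio rest on the assumptions stated with them. The reason to change is freedom from data-driven model choice, not precision.

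**What to change.** - **D.9(c):** delete the imbalance trigger. State that the primary Cox model is stratified by, or adjusted for, age group, sex and commune, plus covariates fixed in advance: baseline cytology group in the dysplasia trial; 1983 screening status in the general population trial; smoking and family history of esophageal cancer in both.
- **D.7:** delete the matching clause, "allow us to adjust for any non-random differences between treatment groups", and keep baseline nutrients for the planned review of outcomes by nutrient status.

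The cost is a few lines of wording. D.10 already provides for recording all of these variables, so no new data collection is needed, and sample size and the stated power are unaffected.

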#### (d.) Stopping Rule

The advantages of a single final analysis of the data and sequential analysis will be combined in a policy of examining the data annually, but not stopping prematurely unless the difference between treatments reaches some extreme level of statistical significance

(e.g., p.001).(34) Otherwise, we will let the trial run its full course of 5 years at the end of which ordinary statistical analysis will be undertaken.

#### 10. Records to be Kept

The CICAMS will develop, in collaboration with NCI, questionnaires and forms needed for the collection, storage, and coding of data. All questionnaires and recording forms used in the study will be developed in both Chinese and English-language versions, and will be reviewed by NCI before being used in the study.

Questionnaires and forms will include the following:

- 1) a brief questionnaire for all study participants, containing personal identifiers, demographic information (age, sex, production brigade), information necessary to confirm the subject's eligibility (for example, whether the person is taking vitamin supplements or other medicines regularly), and several items concerning risk factors such as family history of esophageal cancer patterns of consumption of pickled vegetables or moldy foods and cigarette smoking status;
- 2) a cytology abstract and follow-up form for all those included in the 1983 balloon-swallow mass screening, with space for such information as name, date of birth, sex, commune of residence, study ID if eligible for study, initial cytological diagnosis, and any subsequent cytological diagnosis during the course of the study;
- 3) a form to collate information on all persons considered for the trials, with space for such information as name, date of birth, sex, production brigade of residence, study ID if eligible (or reason ineligible), whether enrolled (or reason if not enrolled), biochemical test status and results, compliance information during the course of the study, and vital status at the completion of the study, with date and cause of death if deceased;
- 4) logs necessary to perform such tasks as:  
assignment of identification numbers, randomization, enrollment, tracking, and distribution of pill packs, reclamation of used pill packs, chronicling of barefoot doctors' visits with participants, noting of pill counts for the purpose of compliance assessment, and recording of dates and causes of death;
- 5) questionnaires and recording forms needed:
  - a) to conduct a biochemical surveillance program to monitor secular and seasonal changes in nutritional status and diet within and among treatment groups, and b) to perform biochemical tests for the purpose of compliance assessment;
- 6) coding sheets listing all of the data collected for each individual, reviewed and edited for completeness and accuracy;

7) logs necessary to maintain quality control of data, including:

a) maintaining a written log or record book of all decisions that affect the design, conduct, or analysis of the study;

b) monitoring the performance of all field staff including

1) repeat interviews by a supervisor for portions of each baseline questionnaire for 2% of all study subjects interviewed, and re-interview of all subjects interviewed by the original interviewer if major discrepancies are found; and

2) having the supervisor independently contact 2% of the participants to verify that the barefoot doctors have delivered the proper pill packs on schedule and have counted unused pills correctly;

c) verifying that all coding of data is accurate;

d) ensuring that all blood, urine, hair, and nail specimens are collected, processed, and stored in a manner that will enable valid analysis for nutrients;

e) ensuring that proper quality control procedures are carried out for all laboratory work, such as performing analyses in duplicate, constructing multiple-point standard curves, and -- simultaneously with the samples from study subjects -- analyzing internal standards, external standards, and "doped" standards to determine recovery, precision, and accuracy;

f) recovering used pill packs with unconsumed pills left in the package. A random sample of these will be returned to the United States for chemical analysis, as a way of verifying the appropriate formulation and assuring that subjects are receiving the correct pills.

